# Relevance of the post-COVID syndrome within rehabilitation (PoCoRe): study protocol of a multi-centre study with different specialisations

**DOI:** 10.1186/s40359-022-00892-8

**Published:** 2022-07-29

**Keywords:** Post-COVID rehabilitation, Treatment effectiveness, Work ability, Fatigue, Post Exercise Malaise

## Abstract

**Background:**

In Patients suffering from post-COVID syndrome, in addition to physical limitations, cognitive limitations, fatigue, dyspnea as well as depression and anxiety disorders may also be present. Up to now (as of May 2022), approx. 514 million people worldwide have been infected with SARS-CoV-2, in Germany this affects approx. 25 million. In Germany, 2.5 million people could potentially be affected by post-COVID syndrome. Post-COVID is thus a highly relevant public health issue. So far, there is no specific causal therapy for the post-COVID syndrome, but with multimodal symptom-oriented rehabilitation, the course can be favourably influenced. However, there is no study yet that focuses on patients in different rehabilitation indications and compares the focal symptomatology and coping strategies as well as the patients' benefit per indication.

**Methods/design:**

As first objective, pulmonal, cardiac, neurological, cognitive or/and psychological functional impairments in rehabilitation patients after COVID-19 disease will be described. The second objective is the differentiated review of the specific rehabilitation measures, in the short term and in the longer term for the purpose of future prognoses and optimisation of therapeutic interventions. This prospective, non-randomised, controlled longitudinal study, plus multi-group comparisons will take place in seven rehabilitation clinics of different specialisations: cardiological rehab, pneumological rehab, neurological rehab, psychosomatic rehab. Within 12 months, 1000 cases across all participating centres will be included. Somatic and psychological testing will be conducted at three measurement points: Admission (t0), discharge (t1), 6-montas Catamnesis (t2). The patients receive the usual care according to the respective rehabilitation priorities, adapted to the special challenges of post-COVID symptoms. Patients of the post-COVID outpatient clinic without rehabilitation will be used as a control group.

**Discussion:**

This study will precisely assess the extent to which subclinical neurological or/and psychological impairments are present in post-COVID-19 rehabilitation and the results will help, developing, providing and evaluating appropriate treatment concepts. This may also have relevant implications for the improvement of physical ability and quality of life in post-COVID-19 patients and increase the probability of return to work.

*Trial registration* Z-2022-1749-8, registered 03. February 2022, https://studienanmeldung.zks-regensburg.de

## Background

In December 2019, the new coronavirus COVID-19 became known and led to a considerable number of worrying cases of illness being reported to the World Health Organisation [1] within a very short time (514 mio. cases worldwide until March 2022; 25 mio. cases in Germany). The WHO declared COVID-19 a pandemic on 11 March 2020. In Germany till March 2022, more than 25 million have been infected. So far, most of the initial infection has been mild to moderate, but late effects in the form of post-COVID syndrome have emerged in both severely affected and less dramatic cases.

The post-COVID syndrome is defined as a condition that usually occurs three months after presumed or confirmed SARS-CoV-2 infection and is characterised by symptoms that persist for at least two months and cannot be explained by any other diagnosis [2]. The most frequently complained symptoms are fatigue, shortness of breath and cognitive impairment, with frequently changing physical complaints and psychological symptoms also occurring in addition and the symptom picture affecting daily functioning in everyday life.

Studies indicate an incidence of post-COVID syndrome of 5–10% in mild to moderate courses of COVID-19 [3, 4], while it can reach 85% in hospitalised patients [5]. The sometimes very large variances in the prevalences found can be explained by the different study populations, symptoms and health problems recorded and follow-up periods. Another crucial aspect is whether the diagnosis of post-COVID syndrome is made on the basis of persistent symptoms associated with COVID-19 or whether the WHO criterion of functional impairment in various areas of life is taken into account. Population-based or sample-based studies, which also include milder courses of the disease, indicate a significantly lower incidence of long-term symptoms: 13.3% of the test-positive study participants had symptoms for longer than 28 days, 4.5% for longer than eight weeks and 2.3% for longer than 12 weeks [4].

Fatigue is the most common symptom, reported by 17.5–72% of post-COVID cases, followed by persistent dyspnoea (10–40%). Psychological problems, chest pain, and smell and taste disturbances can occur in up to 26%, 22% and 11% of patients, respectively [5]. Surprisingly, it has also been shown that people without SARS-CoV-2 infection also report persistent post-COVID-like symptoms [6], which illustrates the low specificity of the complaints and the need for interdisciplinary cooperation between specialists.

In a relevant proportion of those affected, this results in prolonged incapacity to work or, in the worst case, threatens their participation in working life [7]. In view of the SARS-CoV-2 infection figures, this represents a highly relevant problem both for those affected and for the health system [8]. Post-COVID is thus a highly relevant mental health and health care issue [9]. Psychomental limitations in turn interact with the somatic and have a considerable influence on the recovery process in terms of activity and participation and interaction with the social environment. So far, there is no specific causal therapy for the post-COVID syndrome, but with multimodal symptom-oriented interventions, the course can be favourably influenced [10, 11]. This results in the task, especially for rehabilitation, of developing, providing and evaluating appropriate treatment concepts. But with approximately 25 million COVID-19 cases in Germany, an estimate of 10% of those affected by post-COVID syndrome could be 2.5 mio people affected in Germany alone. With an estimate of 2% of those requiring rehabilitation, there would be 500.000 patients. This far exceeds for example the Germany-wide rehabilitation capacities of 150.000 psychosomatic treatment units.

The aim of this study would be to be able to precisely assess the extent to which subclinical somatic or/and psychological impairments are present in post-COVID-19 rehabilitation as soon as possible. It also appears to be of interest whether the rehabilitation success differs according to indication and setting (e.g. pneumology, neurology, etc.) in comparable outcome parameters (e.g. quality of life and functionality, depression and anxiety, somatic symptoms, cognitive performance level, etc.) and consequently whether statements about the (socio-medical) prognosis are possible.

This prospective, explorative, multicentre, mixed-methods study with clinical, standardised examination will include somatic and psychological testing at three measurement points: Admission (t0), discharge (t1), 6-month catamnesis (t2). The study is going to take place in Cardiological rehabilitation, Pneumological rehabilitation, neurological rehabilitation and Psychosomatic rehabilitation. This study is in line with the Stanford Hall consensus statement for post-COVID-19 rehabilitation [12]. In a structured and quantitative way the primary COVID-19, the current post-COVID symptomatology as well as the relevant history on quality of life and functionality will be recorded. Psychological stress, e.g. in the form of depression or anxiety, is assessed via questionnaires, and the cognitive performance parameters relevant to occupational medicine are assessed via an objective neuropsychological test battery. Fatigue and other somatic aspects of physical performance and the muscular/pneumological situation are recorded in the course of medical examinations. We outline that our study protocol is in line with the research agenda of post-COVID fatigue [13]. Furthermore, this study addresses the phenomenon of post-exercise malaise, which is postulated in the line to the post-COVID syndrome, but for which there is a lack of reliable data on whether or how often this phenomenon actually occurs. Apart from that, a training-focused approach is also recommended in this context. In the context of this study, we are therefore not only testing whether rehabilitation is effective, but also whether it is safe for patients with post-COVID syndrome.

The first objective is the description of neurological, cognitive or/and psychological functional impairments in rehabilitation patients after COVID-19 disease.

The second objective is the differentiated review of the specific rehabilitation measures, in the short term and in the longer term (6-month catamnesis) for the purpose of future prognoses and optimisation of therapeutic interventions / the therapeutic offer.

## Research questions

### Primary research question

1.1 Which neurological, internistic and psychosomatic symptoms are present in rehabilitation patients after a COVID-19 disease and how severe are they?1.2 Do the three indications (neurology, pneumology, psychosomatics) differ with regard to the symptom severity of their rehabilitation patients?1.3 How are the symptoms related to each other? Are there specific symptom clusters?

### Secondary research questions

2.1 To what extent do the respective symptoms (dyspnoea or reduced lung function; cognitive impairments; psychological complaints; functional impairments) change during rehabilitation?2.1.1. Does the type of illness behaviour change during rehabilitation?2.2 Are there differences in the different rehabilitative settings?

### Other research questions

3.1 To what extent does the different symptomatology (pneumological, neurological, psychosomatic) correlate with an unfavourable socio-medical evaluation.3.2 Is the type of illness behaviour (avoidance-endurance) a predictor of symptomatology and socio-medical performance assessment?3.2 Is there evidence of post-exercise malaise or other adverse events? Are there patients who deteriorate in the course of rehabilitation? (especially in the Six-Minute Walk Test)3.4.1 Are there medical parameters that can be identified as risk parameters for a unfavourable socio-medical prognosis and a prolonged course of the condition (e.g. spiroergometry, lactate test)?

## Methods/design

### Participants, interventions, and study variables

#### Study setting and recruitment

The envisaged study will take place in seven rehabilitation clinics of different specialisations: cardiological rehabilitation, pneumological rehabilitation, neurological rehabilitation, psychosomatic rehabilitation. All consecutively admitted rehabilitation patients who start rehabilitation as a result of COVID-19 and who meet the eligibility criteria as well as consent to participate in the study will be included. The previous course of infection of the affected persons is irrelevant for the inclusion in the study (e.g. mild symptoms to severe course with hospitalisation) (Fig. 1).

**Fig. 1 Fig1:**
[figure not shown]
Allocation procedure

#### Eligibility criteria

SARS-CoV-2-infection and following post-COVID syndrome: Complaints that are still present more than 12 weeks after the onset of SARS-CoV-2 infection and cannot be explained otherwise.As a consequence of the post-COVID syndrome, at the time of the start of rehabilitation, the presence of functional limitations that may threaten the ability to work.Written informed consent to participate in the study.Aged 18 years or above.Sufficient knowledge of the German language to participate in the study.

#### Interventions

Depending on the symptom focus, rehabilitation patients with post-COVID are treated in specialized rehabilitation clinics. The clinics and their treatment programs are listed below (Table 1). Since post-COVID syndrome is a new clinical picture with multi-organ involvement, attempts are currently being made to assign patients to already existing rehabilitation structures according to symptom focus. As can be seen, the specialisations diverge in the duration and frequency of the therapies, but uniformly cover all essential symptom areas of the post-COVID syndrome with corresponding offers (psychoeducation, exercise, psychotherapy, breathing and relaxation therapy, cognitive training).

**Table 1 Tab1:** Interventions

Clinic	Psychoeducation	Exercise therapy /physical therapy	Relaxation	Psychotherapy		Respiratory therapy	Cognitive training	Creative therapy	Other
				Group	Single session				
*Rehabilitation Centre Todtmoos*									
Pneumological departement	1 × per rehabilitation/60 min *Post-COVID Pneumology* 1 × per rehabilitation/90 min *Post-COVID psychosomatic perspective* 1 × per rehabilitation/60 min *Introduction to exercise therapy*	3 × per week/30 min exercise therapy 5 × per week/30 min monitored ergometer training	3 × per week/30 min relaxation therapy 1 × per week/60 min QiGong (as needed)	2 × per rehabilitation/90 min	1 × per rehabilitation/45 min	4 × per week/30 min	As needed (Freshminder)	Ergotherapy (as needed) Art therapy (as needed)	1 × per week/60 min pacing-group Olfactory training (as needed) Nutrition advice (as needed) Social service (as needed)
Psychosomatic Department		1 × per week/90 min exercise therapy 4 × per week/30 min monitored ergometer training	2 × per week/30 min relaxation therapy	2 × per week/90 min 1 × per week/60 min	1 × per week/30 min	2 × per week/30 min		1 × per week/90 min Ergotherapy 1 × per week/90 min Art therapy	
Psycho-pneumological departement		2 × per week/60 min exercise therapy 4 × per week/30 min monitored ergometer training	2 × per week/30 min relaxation therapy	3 × per week/90 min	1 × per week/60 min	5 × per week/30 min		1 × per week/90 min Ergotherapy	
*Alpcura Clinic*									
Pneumological rehabilitation All Patients	1 × per rehabilitation/60 min *Post-COVID* 1 × per rehabilitation/30 min *social law / medicin* 3 × per rehabilitation/60 min *diet* 1 × per rehabilitation/30 min *Hygiene training*	2 × per week/30 min monitored ergometer training 2 × per week/30 min strenght training 2 × per week/30 min Vibration platform training 3 × per rehabilitation 45 min back school 1 × per week 45 min Balance training (as needed)	2 × per week/30 min Relaxation therapy 1 × per week/20 min Hydrojet massage 1 × per week/25 min infrared treatment	1 × per week/60 min (as needed)	1 × per week/30 min (as needed)	2 × per week/45 min	3 × per rehabilitation/ 60 min	1 × per rehabilitation/ 60 min Daily life training (as needed) 3 × per rehabilitation/ 60 min technique/skills training (as needed)	30 min Water stepping (as needed) Social service (as needed) 1 × per week/ 45 min conversation group „think positive “ (as needed)
Low capability patients		3 × per rehabilitation/ 45 min. Stair climbing under physiother. Guidance and pulsoxymetric monitoring 1 × per week functional training						1 × per rehabilitation (or more) Ergotherapy	
More powerfull patients		1 × per rehabilitation/45 min Facia training 1 × per week/45 min spinal gymbastics 1 × per week/45 min cardiovascular training 1 × per week/ min Nordic Walking	2 × per week/45 min Relaxation therapy 3 × per week/30 min QiGong					None	
*Rehabilitation Clinic Seehof, Teltow *									
Psycho-cardiolocical rehabilitation	1 × per rehabilitation/60 min *Post-COVID* 1 × per rehabilitation/30 min *Introduction to exercise therapy* Mulltiple times per rehabilitation/60 min *psychosomatic or cardiological topics* 1 × per rehabilitation/45 min *Introduction cognitive training*	2 × per week/30 min exercise therapy „COfit “ 2 × per week/30 min monitored ergometer training 2 × per week/45 min Nordic Walking (as needed) 2 × per week 30 min aqua fitness (as needed)	2 × per week/45 min Relaxation therapy 1 × per week/60 min QiGong Hydrojet massage (as needed)	2 × per week/90 min	2 × per week/30 min or 1 × per week/60 min	2 × per week/30 min	2 × per week/60 min Group 3 × rehabilitation/30 min Single session Accompanying training tasks	1 × per week/ 90 min Ergotherapy Art therapy (as needed) Therapeutic dance (as needed)	Nutrition advice (as needed) Social service (as needed) 2 × per week/ 30 min Mindfulness group Aroma therapy (as needed)
*Gelderland Clinic*									
Psychosomatic rehabilitation	1 × per rehabilitation/60 min *Post-COVID and Naturotherapy* 2 × per rehabilitation/60 min *Naturotherapy for stress at work* 1 × per rehabilitation/60 min *Introduction cognitive training* 1 × per rehabilitation/30 min *Introduction cognitive training Freshminder*	1 × per week/45 min monitored strenght training 1 × per week/45 min monitored coordination training or 1 × per week/30 min aqua fitness 1 × per week/60 min Walking	1 × per week/45 min QiGong or Yoga 1 × per week/45 min meditative moving	2 × per week/ 75 min 1 × per week/ 60 min	1 × per week/30 min	2 × per week/30 min Group 2 × per rehabilitation/ 30 min single session	2 × per week/30 min Group	1 × per week/45 min meditative dancing or 1 × per week/45 min meditative forest bathing 1 × per week/30 min dew stepping Ergotherapy (as needed)	Nutrition advice (as needed) Social service (as needed) 1 × per week/ 30 min Mindfulness group Aroma therapy (as needed)
*Schmieder Clinics*									
Neurological rehabilitation *Note.* Patients have approx. 19–21 therapy sessions per week in an individual therapy plan	1 × per rehabilitation *Post-COVID* Multiple times per rehab, different topics like *smoking cessation, dietetics, overweight, muscular deficits*	After performance level assessment: Stamina training Strength training Vibration platform training	As needed (PMR)	As needed	As needed	Breathing therapy group Guided self-exercise training with breathing therapy device Oxygen therapy (as needed)	Assessment and training as needed	Daily life training (as needed) motor-functional training (as needed)	Olfactory training (as needed) Nutrition advice (as needed) Social service (as needed)
*Clinic Westerwald*									
Neurological rehabilitation *Note.* Patients have a very individual therapy plan	1 × per rehabilitation *Post-COVID* Multiple times per rehab, different topics like *fatigue, headache, dietetics,* *Smoking cessation*	After performance level assessment: stamina training strength training Vibration platform training	As needed (PMR, autogenic training)	none	1 × per week/ 60 min (as needed)	As needed	Assessment and training (CogniPlus) as needed	Compensatory and memory strategies (as needed)	Olfactory training (as needed), including Kaiteki maneuver with local application of vitamin A Speech therapy (as needed) Social service (as needed

The rehabilitation concepts of the neurological clinics are so individual that it is not possible to make any useful and schematic statements about therapy times in advance

### Control group (post-COVID outpatient clinic Regensburg)

This is a matched control group or comparative data from Regensburg Post-COVID Outpatient Clinic. The patients in the Regensburg post-COVID outpatient clinic meet the same inclusion criteria as the study cohorts of the rehabilitation clinics and receive the same diagnostic examinations. Due to the ambulance setting, which focusses only on the diagnostic process, there is no intervention.

#### Study variables

The study-related examinations/tests are carried out by a psychological specialist upon admission to rehabilitation and discharge. If spiroergometry is carried out on the patients, this is done by the specialist staff and the findings are added to the study documentation by the local study assistant. At discharge, a treatment recommendation is made according to the findings available at that time, e.g. short versus long neuro-rehabilitation (in addition to the somatic, psychosomatic and/or integrated rehabilitation). Within the framework of the catamnesis, all further medical measures that were used during the observation period are recorded retrospectively.

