#### Neurological assessment

##### Montreal cognitive assessment (MoCA)

The MoCa test is performed by healthcare professionals to detect early stages of dementia and mild cognitive impairment and to distinguish them from “normal” senile forgetfulness. The MoCa test is significantly more accurate in detecting mild forms of dementia with only slightly impaired abilities than other well-established procedures such as the MMST, which is often used in dementia diagnostics. The test, which lasts about 10 min, contains 30 questions that test various cognitive abilities such as memory, language, contextual thinking, attention and concentration, behaviour, arithmetic, temporal and spatial orientation and the ability to recognise complex shapes and patterns. Scores of 26 to 30 points are considered unremarkable, no limitations, 6 to 25 points indicate at least mild cognitive impairment, and 0 to 5 points are interpreted as extreme mental impairment [20].

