##### TAP-test

The Test Battery for Attention (TAP) is a software package and offers a collection of different test procedures with which the various sub-aspects of attention can be recorded in a differentiated manner and also cover related aspects of visual perception. Subtests are Alertness, working memory, sustained attention, flexibility, divided attention and go/nogo paradigm. The test takes about 45 min to complete [21] (Table 3).

**Table 3 Tab3:** Overview of the TAP subtests used

Subtest	Cognitive domain	Information about
Alertness	Intensity of attention	Basal reactivity, general processing speed, reaction stability, distinction tonic and phasic alertness
Working memory	Executive functions, control of the focus of attention	Ability to continuously update the content of working memory
Sustained attention	Intensity of attention	Longer-term maintenance of attention with high target stimulus density
Divided attention	Attentional selectivity, focused attention, visuo-spatial attention	Ability to focus attention on two tasks simultaneously
Alertness	Intensity of attention	See above

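### Repeating MoCA, TAP and the walk test at admission and discharge lets retest gain enter the within-patient readings, and the control contrast removes it only if controls are retested on a matching schedule

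*Protocol article*

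**What the plan says.** On timing, the Study variables section of the protocol article states "The study-related examinations/tests are carried out by a psychological specialist upon admission to rehabilitation and discharge", and the abstract states "Somatic and psychological testing will be conducted at three measurement points: Admission (t0), discharge (t1", followed by a third point at six months. The length of stay, and so the interval from t0 to t1, is not given.

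The tests include the MoCA ("The test, which lasts about 10 min, contains 30 questions"), the attention battery TAP (about 45 minutes) and the six-minute walk test (6MWT), scored as distance in metres. On the MoCA, "Scores of 26 to 30 points are considered unremarkable, no limitations, 6 to 25 points indicate at least mild cognitive impairment".

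Two research questions draw on repeated results within the same patients. Question 2.1 asks "To what extent do the respective symptoms (dyspnoea or reduced lung function; cognitive impairments; psychological complaints; functional impairments) change during rehabilitation". Among the other research questions is "Are there patients who deteriorate in the course of rehabilitation? (especially in the Six-Minute Walk Test". Neither names a comparator. The Background adds that the study tests both effectiveness and safety.

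The Treatment effect section compares change scores between the rehabilitation clinics and the outpatient control group, using mixed models over all three measurements. The Control group section says that controls undergo the same examinations, but leaves open whether they are a matched group or comparative data. It adds: "Due to the ambulance setting, which focusses only on the diagnostic process, there is no intervention". No retest schedule for controls appears in the text. The study-procedure figure is not reproduced in the copy reviewed.

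**The concern.** On a performance test, the second result contains true change plus whatever the patient gained by having met the task before. A difference from admission to discharge in one group cannot separate the two.

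Two conclusions are exposed. The first is the answer to question 2.1 for cognition: in a sample of this size, a small retest gain is enough to give a clearly significant mean improvement. The second is the safety reading. A familiarity gain in walking distance offsets a true loss, so fewer patients appear to have deteriorated.

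**Working it through.** The article gives no retest figure, no standard deviation and no power calculation, so there is no stated figure to reproduce. What follows is illustration under stated assumptions.

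**Inputs from the article:** 1000 cases; seven clinics; significance at p<0.05; MoCA cut between 25 and 26.

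**Assumed:** two-sided testing; all 1000 cases in rehabilitation; equal split over clinics (1000/7 ≈ 143); true mean change of zero; the retest gains, retest correlations and control sizes shown below.

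**1. Uncontrolled mean change, gain g in SDs of the change score.**
P(significant) = Φ(g√n − 1.96) + Φ(−g√n − 1.96). The smallest observed mean gain reaching p<0.05 is 1.96/√n.

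| n | Smallest gain | g = 0.05 | g = 0.1 | g = 0.2 | g = 0.3 |
|---|---|---|---|---|---|
| 1000 | 0.062 | 0.353 | 0.885 | 1.00 | 1.00 |
| 143 (one clinic) | 0.164 | 0.092 | 0.223 | 0.667 | 0.948 |

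**2. The same, with the gain in SDs of the test score.**
SE of mean change = √(2(1−r)/n). For n = 1000 and r = 0.6, 0.7 and 0.8, SE = 0.0283, 0.0245 and 0.0200. A gain of 0.1 SD then gives z = 3.5, 4.1 and 5.0, with P(significant) = 0.94, 0.98 and 0.999. These values exceed the 0.885 of step 1 only because the unit differs: for r above 0.5 the change score has a smaller SD than the test score.

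**3. Contrast with controls.**
Let d be the difference in retest gain between rehabilitation patients and controls, in SDs of the change score. SE = √(1/1000 + 1/n_c), with no true effect.

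| Assumed n_c | SE | d = 0 | d = 0.1 | d = 0.2 |
|---|---|---|---|---|
| 50 | 0.145 | 0.05 | 0.106 | 0.281 |
| 100 | 0.105 | 0.05 | 0.159 | 0.479 |
| 200 | 0.077 | 0.05 | 0.252 | 0.733 |

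With equal gains the error rate is nominal. With unequal gains, for example if controls are tested once or at another interval, it is not.

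**4. Individual deterioration.**
The article states no threshold. Suppose it were a change below −0.5 SD of the change score, with change distributed N(g, 1). The share flagged is Φ(−0.5 − g):
- g = 0: 30.9%
- g = 0.2: 24.2%
- g = 0.5: 15.9%

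If the limit is shifted by the gain (−0.5 + 0.2 = −0.3 when g = 0.2), the share returns to Φ(−0.3 − 0.2) = Φ(−0.5) = 30.9%. Without such a shift, a contrast of group means leaves these counts untouched.

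Measurement error works the other way. Against a limit of zero, 50% are flagged at g = 0 and 42.1% at g = 0.2, although true mean change is nil. A usable limit therefore has to allow for both retest error and gain.

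**5. MoCA classification.** On the article's own cut, a gain of one point moves a patient from 25 (at least mild impairment) to 26 (unremarkable).

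**The case against.** The strongest reply is that the only inferential plan for change is a contrast with controls who undergo the same examinations, and that this removes a common retest gain. That is right for group means. A reader might infer that the plan is unprotected altogether, or that practice is bound to be reported as improvement. The article supports neither. It does not say that controls lack a second test, and its model presupposes three measurements. What it leaves open is when controls are retested: its time points are named by admission and discharge, which an outpatient diagnostic clinic does not have, and the controls may be comparative data only.

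A second reply is that test versions and familiarisation procedures belong in a full protocol or test manual. This also stands in part. The article does not say that one MoCA form is reused, and its silence on TAP practice runs is no finding. The point rests on what is written: repeated testing, two questions without a comparator, and an unstated control schedule.

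A reader might also infer that computer-based cognitive training biases the comparison of settings in question 2.2. Table 1 does not bear this out. The named training software is mostly listed as needed, training is part of the treatment, and a retest gain common to all clinics cancels between them.

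Finally, adverse events and malaise are logged separately, and no counting rule for deterioration is stated. It therefore cannot be said that the reported count would be too low overall, only that retest gain pushes it downwards.

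**Conclusion.** The point holds in limited form. Retest familiarity can inflate the t0–t1 improvement on MoCA, TAP and 6MWT and can lower the number of patients seen to deteriorate. The control contrast repairs group means only under a matching retest schedule, which the text does not state, and does not repair individual classification.

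The size is unknown. The probabilities above show how little gain is needed at n = 1000. They do not show that such a gain will occur: they rest on assumed gains, correlations, control sizes and a deterioration limit, and the retest interval is not given. The study calls itself explorative, and question 2.1 asks about extent, so the main harm would be to interpretation. The remedy is cheap enough that it should be adopted.

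**What to change.** - **Test forms.** Use parallel MoCA forms at t0, t1 and t2, in an order balanced across patients.
- **Control schedule.** State whether and when controls repeat MoCA, TAP and 6MWT, and match the intervals to the rehabilitation group.
- **Claims.** Base any statement of a rehabilitation effect on these three tests on the contrast with controls tested at matching occasions. Report the uncontrolled t0–t1 difference as change including retest gain.
- **Deterioration.** For analysis only, count a patient as deteriorated when change < ĝ − k × SD_change. Here ĝ is the expected retest gain, SD_change reflects retest error, and k is fixed in advance. Estimate ĝ and SD_change from repeat-tested controls or, failing that, show the count over a stated range.

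**Cost.** Different MoCA sheets per visit and a few lines of text, with no extra visit for rehabilitation patients. If controls are not already to be retested at matching times, those sessions must be added or the effect claims dropped. Parallel MoCA forms may differ slightly in difficulty, which the balanced order averages out. They do not address task familiarity in TAP or 6MWT, for which the matched control schedule is needed.
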